### 3. STUDY DESIGN

This study will be a prospective interventional study, starting 1 January 2016, and planned until 31 December 2017.

A pre-operative clinical pathway is set up for patients of seventy years or older with surgical indication for colorectal cancer or abdominal aortic aneurysm, the 70 PLUS outpatient clinic in our surgery department. Within one week since indication for surgery is decided, a nurse practitioner, a physiotherapist and a dietician will see these patients and all factors of frailty will be investigated. If needed, a geriatrician will also see the patient for complete geriatric assessment and advice during admission to prevent delirium (criteria for CGA is described in *chapter 6.2 study procedures*). Diet advice and physical exercises will be given to all patients in need. Patients must follow these advices and keep a diary.

All patients aged  $\geq 70$  years will be included in this study to follow our pre-operative clinical pathway for optimisation. Also patients, who are not clinically fit to wait for 5 weeks will be included and optimised until surgery.

We propose an optimum preparation time during 5 to 6 weeks till surgery. This is based on the SONCOS quality guidelines 2015 for colorectal cancer, in which a maximum delay of 6 weeks is proposed from pathology result until surgery (Addendum: SONCOS quality guidelines 2015 for colorectal cancer ).

Prospectively gathered data of all cases will be compared to a retrospective, historical, control group of comparable patients from 1 March 2013 till 1 March 2015.

These patients have not been evaluated for factors of frailty in advance. This is a cohort of patients of the age  $\geq 70$  years who received treatment for colorectal cancer with or without neo-adjuvant therapy (radiation or chemotherapy). Both open and laparoscopic surgery will be included.

Also patient who received treatment for abdominal aneurysm of the age  $\geq 70$  are included. These patients underwent an EVAR or open repair. (Complete description of the pathway in the retrospective group is described in *chapter 6.2 Study procedure* and addendum *Amphia protocol Colonchirurgie*)

Only electively planned surgery is included, all emergent or urgent surgical procedures are excluded.

Data of patients in both groups will be gathered in the Amphia Hospital Breda, the Netherlands.

All information will be gathered using Hyperspace Version IU4 (Epic, Inc., Verona, WI).

The historical patient group is based on patients admitted to the Amphia Hospital Breda in 2013 till November 2015. All data is gathered retrospectively but due to the use of the electronic patient file (Hyperspace Version IU4 (Epic, Inc., Verona, WI)) data was saved prospectively. No recent major changes have been made to indicate new procedures or pathways for the interventional care group compared to the historical patient group. The historical group will be comparable to the interventional care group in age ( $\geq 70$  years), ethnicity, gender and indication for surgery. Patients with emergent or urgent surgical intervention won't be included in this study, neither in the historical cohort. All patient who underwent neo adjuvant chemo – and / or radiotherapy are included.

However no questionnaires are undertaken in the historical group, hence the lack of prospective knowledge concerning dementia (scored by MMSE), quality of life or depression scale.

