**Sample size calculation**

To reduce the percentage of delirium from 15% to 7,5%, with a power of 80% with 5% two-sided significance level, a 50 -50 trial, needs 550 patients, or 275 patient per study arm.

We propose to make a comparison to a retrospective control group of patients studied between 2012 and 2014 in the Amphia Hospital, Breda. [1]

We aim to include 275 patients in the prospective study, which is feasible during approximately 2 years of accrual.

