## 5. TREATMENT OF SUBJECTS

This prospective study is set up as an outpatient clinical pathway in which we intend to intervene in the usual pathway until operation. Within one week after setting indication for surgery, patients will be assessed. A nurse practitioner, a dietician and a physiotherapist will see the patients and if necessary a geriatrician will be involved (specific criteria for consulting dietician or geriatrician are defined in chapter 6.2 *Study procedures*).

In the usual pathway, patients are seen by the surgeon and are planned for surgery as soon as possible (which is the case in the retrospective group).

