### 8.2 Secondary study parameter(s)

Secondary we will measure mortality within one year after surgery. Also duration of hospital stay, ICU admission, and complications during hospital stay will be investigated.

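### OUTO patients enter at the decision to operate and controls at completed elective surgery, so events during the longer pre-operative wait can fall outside the comparison

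*Protocol*

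**What the plan says.** **Entry, OUTO.** Patients are selected at the multidisciplinary meeting (section 4.1). They are seen at the 70 PLUS clinic within a week of the indication (sections 3 and 5) and sign consent there (section 9.2). The intended preparation is 5 to 6 weeks (section 3).

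**Entry, controls.** Section 3 describes patients aged 70 or older who had already received treatment for colorectal cancer or an aneurysm. Of the aneurysm patients it says: "These patients underwent an EVAR or open repair". Section 5 gives their waiting time only in words: "In the usual pathway, patients are seen by the surgeon and are planned for surgery as soon as possible".

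**Exclusion.** Section 3 says "Only electively planned surgery is included, all emergent or urgent surgical procedures are excluded", and later "Patients with emergent or urgent surgical intervention won't be included in this study, neither in the historical cohort". The exclusion criteria in section 4 define emergent as within 12 hours of admission and urgent as 12 to 72 hours. Section 8 says both groups are selected for analysis on one set of criteria.

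**Mortality.** Section 8.2: "Secondary we will measure mortality within one year after surgery". The 6-month mortality in the Summary, section 2 and section 6.7 is given no starting point.

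**The concern.** The intervention lengthens the time between the decision and the operation. In that time a tumour may obstruct, an aneurysm may become symptomatic, or a patient may die or become inoperable. A control could enter the historical cohort only by reaching elective surgery. An OUTO patient enters before anyone knows whether that will happen.

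If converted patients are then dropped and the mortality clock starts at surgery, the OUTO group is reduced to patients who came through the longer wait still elective. The patients lost are likely to be at higher risk, so the comparison can favour OUTO. The wait is also where the pathway itself could plausibly do harm, and no endpoint compares it between cohorts. The one-year safety check in section 6.7 uses the same historical group and so has the same gap.

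**Working it through.** **1. The two cohorts side by side**

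| | OUTO | Historical |
|---|---|---|
| Identified by | meeting decision, consent at the clinic visit (4.1, 9.2) | elective treatment already received (3) |
| Wait | 5 to 6 weeks intended (3) | no duration given (5) |
| Urgent or emergent procedure | excluded (3, 4) | excluded (3) |
| One-year mortality | from surgery (8.2) | from surgery (8.2) |
| Dies or is never operated on | enrolled, but has no surgery date | cannot be in the cohort |

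The same exclusion in both columns does not make the cohorts alike, because the time at risk of meeting it differs. Urgency is defined in hours from admission. For an outpatient prepared over weeks, that is known only at the surgical admission, after enrolment.

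**2. The plan's own figure**

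The inputs are "To reduce the percentage of delirium from 15% to 7,5" percent, "with a power of 80% with 5% two-sided significance level". The plan concludes that the study "needs 550 patients, or 275 patient per study arm".

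With unpooled variance, n = (1.960 + 0.842)² × [0.15 × 0.85 + 0.075 × 0.925] / 0.075² = 7.849 × 0.196875 / 0.005625 = 274.7, so 275 per group. The pooled formula gives 278, and power at 275 is 79.6%. The sample size reproduces and is not at issue.

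**3. Scale for mortality**

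The inputs are from section 1: 6-month mortality of 20% with delirium and 3% without.

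- At 15% delirium: 0.15 × 20% + 0.85 × 3% = 5.55%, or 15.3 deaths per 275.
- At 7.5% delirium: 0.075 × 20% + 0.925 × 3% = 4.275% (4.28%), or 11.8 deaths per 275.
- Implied gain: 1.275 points, or 3.5 deaths per 275.

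Let f be the excess share of OUTO patients lost during the wait, over any such loss in controls, and m their 6-month mortality. The gain is cancelled when f = (5.55% − 4.275%) / (m − 4.275%).

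- All lost patients die (m = 100%): f = 1.275 / 95.725 = 1.3%, or 3.7 patients, so about four.
- Half die (m = 50%): f = 1.275 / 45.725 = 2.8%, or 7.7 patients, so about eight.

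**4. Scale for delirium**

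Here f covers only patients who convert and are operated on. Let d be their delirium rate. The OUTO rate with them kept is (1 − f) × 7.5% + f × d. Both f and d are assumptions: d = 30% is illustrative, and 50% is the upper figure in section 1 for hospitalised elderly. Controls stay at 15%.

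| f (patients of 275) | d = 30% | d = 50% |
|---|---|---|
| 1% (2.75) | 7.7%, power 77% | 7.9%, power 74% |
| 3% (8.25) | 8.2%, power 71% | 8.8%, power 62% |

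**The case against.** A reader might infer that the protocol orders removal of anyone who becomes urgent after enrolment. It does not.

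- The exclusion criteria are worded for potential subjects, which is screening language.
- The specific withdrawal criteria in section 6.4 do not list conversion.
- Section 7.2 keeps patients with an adverse event in the database. An obstruction needing admission would meet its definition of a serious adverse event.
- Section 6.6 retains complication and mortality data after withdrawal.
- Sections 3 and 4.1 keep patients who cannot wait five weeks, provided surgery is still elective, expressly for comparability.

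These points stand, and they mean that some of the data will exist. They do not settle the analysis. Section 3 excludes procedures without reference to when they became urgent, and section 8 applies the criteria at selection for analysis. Retained pre-operative deaths have no counterpart among controls chosen by completed treatment. Adverse-event recording describes OUTO alone, and section 7.2 exempts deaths from the normal course of illness from SAE notification.

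A second objection is that controls also lose patients under the same rule. That is correct, so only the excess loss matters, and it cannot be computed without the historical waiting time.

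A third is that the handling of converted patients may be left to an analysis plan. But cohort entry, the exclusion and the one-year mortality clock are fixed in the protocol.

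**Conclusion.** The point holds as a defect of cohort definition. The entry points differ, the exclusion is not limited to status at the decision, one-year mortality starts at surgery, 6-month mortality has no origin, and events before surgery are not compared. The likely direction favours OUTO.

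The size is unknown. The documents give no conversion rate, pre-operative death rate or historical wait. Mortality is the sensitive endpoint: an excess of about four uncounted pre-operative deaths in 275 would offset the whole gain implied by the protocol's own rates. That calculation assumes mortality changes only through delirium.

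The effect on delirium is likely smaller. With 1% to 3% excess conversion and a 30% to 50% rate, 7.5% becomes 7.7% to 8.8%, still well below 15%. A reader might treat everyone lost during the wait as a potential delirium case and obtain a larger effect. That is not supported, since patients never operated on cannot have postoperative delirium. Nor do the documents show a bias in OUTO's favour on every endpoint, for example on hospital or ICU stay.

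**What to change.** - State that urgent or emergent status is judged at the date of the multidisciplinary decision in both cohorts. Both pathways include that meeting (sections 4.1 and 6.2).
- Keep every enrolled OUTO patient in the analysis, including those later operated on urgently or never operated on.
- Build the historical cohort from the same decision date where the electronic file allows.
- Count 6-month and one-year mortality from that date.
- Analyse postoperative delirium in operated patients, including conversions.
- Report pre-operative deaths, conversions and cancellations by cohort. Consent follows the meeting, so also log OUTO patients selected but lost before the clinic visit.

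If historical meeting records prove incomplete, report these events for OUTO, add a sensitivity analysis over a range of excess loss, and state that the comparison is conditional on reaching elective surgery.

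The cost is protocol wording and retrieval of historical records, whose completeness the protocol does not establish. No extra patients or visits are needed. The OUTO result may look less favourable.

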## 1. INTRODUCTION AND RATIONALE

The population of people above 65 years old is expected to double in the next 35 years. The increase of age is associated with an increase in need for medical care and number of patients requiring surgery. A higher rate of post-operative complications, like a delirium (37%), longer hospital stay, ICU admission, and mortality is associated with increasing age.[1, 2]

In our hospital, within the population of 70 years or older, approximately 85 patients per year undergo surgery for colorectal cancer and about 50 patients per year undergo surgery for abdominal aortic aneurysm. We expect an increase in the number these surgical procedures performed during the coming years (also due to the implementation of screening programs).

A delirium is often a fatal disorder. It affects as much as 50 % of the elderly people who are hospitalised. In the population described above, the incidence of a delirium is about 15%. The 6-month mortality is increased within patients with a postoperative delirium (20%) versus no delirium (3%). [3] In short a delirium is a common complication after surgical intervention and results in a significant decrease in quality of life, an increased rate of complications, mortality and additionally is associated with high costs. Therefore a delirium holds essential health relevance.

The cause of a delirium can be the result of a single factor but is mostly a combination of different factors at once. Many factors have been identified and validated to be an independent cause of a delirium. These factors of frailty are for example the patient's nutritional state, physical health, the use of medication, the patient's mental state, laboratory results (such as anaemia and renal function), delirium in patient's history, visual and hearing impairment.

At the moment physicians are already more aware of these frail elderly and these factors of frailty but it is only tackled at admission in hospital or at long care facilities. A delirium is preventable in 30 to 40 % of the cases. Therefore the Hospital Elder Life Program (HELP), a worldwide non –pharmaceutical program, is implemented. This program starts at admission and is proven to be effective to prevent a delirium. [3-5] Another recent study, for patients with an acute hip surgery, shows that specific ortho – geriatric care during admission improves the outcome 4 months after surgery. [6]

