## 6.2 Study procedures

### Standard Care

Standard pathway until surgery contains a visit to the outpatient clinic of either a gastroenterologist or a vascular surgeon to diagnose patients' condition. Patients will be discussed during multidisciplinary meeting, where the decision to operate is made. Next patient will be seen by their surgeon give explanation about the surgical procedure and to screen if patient is fit for surgery. Normal surgical preparations are done. At admission patient will be screened for delirium by a ward nurse. If necessary a dietician or geriatrician will visit. Standard care during admission is applied. (Addendum *Amphia protocol Colenchirurgie*)

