### **6.5 Replacement of individual subjects after withdrawal**

Patients withdrawn from this study will not be replaced.

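### The claim that care was stable between the historical and OUTO periods is unsupported, and the primary analysis would count any background fall in delirium as an OUTO effect

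*Protocol*

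**What the plan says.** Section 3 compares a prospective cohort (1 January 2016 to 31 December 2017) with a retrospective cohort from the same hospital. There is no concurrent control. On comparability of care it says: "No recent major changes have been made to indicate new procedures or pathways for the interventional care group compared to the historical patient group". No dates or data accompany this.

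The control period appears in three forms: 1 March 2013 to 1 March 2015, and 2013 to November 2015 (both in section 3), and 2012 to 2014 (Sample size calculation).

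Section 1 reports that HELP has been implemented and adds: "This program starts at admission and is proven to be effective to prevent a delirium". It also says: "At the moment physicians are already more aware of these frail elderly and these factors of frailty". Neither remark is dated, and the HELP sentence does not name this hospital. For inpatient management, the Standard Care text in section 6.2 says only "Standard care during admission is applied" and points to an addendum.

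Section 8 makes the primary analysis a logistic regression on patient-level covariates (age, gender, comorbidity, medication, BMI, home situation and others), with POSSUM and Charlson scores also considered. Calendar time and ward care are not among the terms listed.

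**The concern.** Every control is treated before every OUTO patient, so treatment group and period cannot be separated. A covariate describing the patient cannot remove a change in how the ward prevents or detects delirium. Attribution to preparation before admission therefore rests on the stability sentence alone.

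That sentence needs support because the protocol itself names an inpatient programme that acts on the primary endpoint. If HELP or similar ward practice began or matured between the control years and 2016-2017, delirium could fall with no contribution from the outpatient pathway, and the primary odds ratio would show it as an OUTO effect. The one-year safety comparison in section 6.7 uses the same historical group, so improving background care could also mask harm.

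**Working it through.** **Inputs.** Sample size calculation: "To reduce the percentage of delirium from 15% to 7,5" percent, "with a power of 80% with 5% two-sided significance level, a 50 -50 trial, needs 550 patients, or 275 patient per study arm". Section 1: the protocol regards 30 to 40% of delirium as preventable. The drift sizes below are assumptions, since the documents report no trend in incidence.

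**The plan's own figure.** n = (1.960 + 0.842)² × (0.15×0.85 + 0.075×0.925) / 0.075² = 274.7, so 275 per group. The pooled-variance formula gives 278, and power with 275 is 79.6%. The stated sample size reproduces and is not at fault.

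**Drift with no OUTO effect.** Take controls at 15% and the prospective group at a drifted rate p, with n = 275 each. With d = 0.15 − p and p̄ the mean of the two rates:

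- SE0 = √(2p̄(1−p̄)/n)
- SE1 = √((0.15×0.85 + p(1−p))/n)
- P(significant benefit) = Φ((d − 1.96×SE0)/SE1)

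A 30% relative fall gives 15% × 0.7 = 10.5%. A 40% fall gives 15% × 0.6 = 9%. The rates 13.5% and 12% are milder cases.

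| Drifted rate | d | SE0 | SE1 | z | P(significant benefit) | Exact binomial |
|---|---|---|---|---|---|---|
| 15% (no drift) | 0 | – | – | −1.96 | 2.5% | 2.5% |
| 13.5% | 0.015 | 0.0298 | 0.0298 | −1.457 | 7% | 7% |
| 12% | 0.030 | 0.0291 | 0.0291 | −0.931 | 18% | 17% |
| 10.5% | 0.045 | 0.0284 | 0.0284 | −0.379 | 35% | 35% |
| 9% | 0.060 | 0.0277 | 0.0276 | 0.206 | 58% | 58% |

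**Partial drift.** If background care alone brought the rate to 12% and OUTO took it to 7.5%, then 3 of the 7.5 points (40%) would be misattributed. The remaining 4.5-point effect would need 681 per group against a concurrent control; 275 per group gives 43% power.

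**Can a time-trend model repair this?** Consider a logistic model with a common calendar slope and an OUTO step, 275 per group, even accrual, no true trend and the full effect. The odds ratio is (0.075/0.925)/(0.15/0.85) = 0.459, with log −0.778. Standard errors come from the expected information matrix, and power = Φ(0.778/SE − 1.96).

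| Analysis | SE of log OR | Expected 95% CI | Power |
|---|---|---|---|
| No time term | 0.284 | 0.26 to 0.80 | 78% |
| Slope, controls March 2013 to March 2015 | 0.725 | 0.11 to 1.9 | 19% |
| Slope, controls 2013 to November 2015 | 0.536 | 0.16 to 1.3 | 30% |

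The control group supplies only about 0.15 × 275 = 41 events. Over a two-year window that is about 5 per quarter or 10 per half-year.

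**The case against.** A reader might infer that the protocol contradicts itself by claiming unchanged care while describing changing care. The text does not support that. HELP and the greater awareness are undated and appear in a rationale written before the study began. Both may have applied equally to the controls, in which case the 15% baseline already includes HELP's effect.

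A reader might also cite the preparation window ("This is based on the SONCOS quality guidelines 2015 for colorectal cancer") or the screening programmes as signs of better care. Neither serves. The guideline concerns the maximum delay to surgery and is used to set the OUTO window. Screening is mentioned as a reason for more operations and bears at most on case mix, which the listed covariates are meant to address.

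The addendum describing ward care was not available, so the brevity of the Standard Care text does not show that HELP is left undescribed. The 9 to 10.5% scenarios assume that all delirium called preventable disappears through background care, which is an upper range and not a forecast. Trend tables and sensitivity models may also sit in an analysis plan that was not available.

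All of this stands. What remains is that the protocol itself fixes the comparator, asserts stability without evidence, names a primary model without a time term and gives three control windows. Until one window is fixed, nobody can establish which background care the controls received.

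**Conclusion.** The stability statement is an unsupported assumption on which the causal reading of the primary result depends. It has not been shown to be false. If background care alone lowered delirium from 15% to an assumed 12%, 10.5% or 9%, a significant benefit would appear about 18%, 35% or 58% of the time with no OUTO effect, against a nominal 2.5%. These probabilities are conditional on the assumed drift and on 275 per group in an unadjusted comparison. They do not estimate this trial's actual error rate.

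It would also be wrong to infer that OUTO should be judged by whether its effect stays significant after adjustment for a time trend. With the full effect present and no trend, that rule would reject it 70 to 81% of the time. The historical design can stay, but its central assumption should be documented, examined and reflected in the conclusion.

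**What to change.** 1. Reconcile the three control windows into one and use it throughout.
2. Replace the stability sentence with the dates, at this hospital, on which HELP and other delirium-related ward protocols began or changed, set against that window.
3. If any began within or after the window, use controls treated under the same inpatient protocol as the comparator, or report results split at that date.
4. Tabulate delirium by calendar period. Half-years suit about 41 control events better than quarters.
5. Report a logistic model with a calendar-time term as a supportive sensitivity analysis only. State its power of about 19 to 30% for the full hypothesised effect, and do not make the conclusion depend on its significance.
6. Word the conclusion as a before-after association that assumes stable background care.

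The cost is a few protocol lines and a little more analysis, with no extra patients to recruit. Step 3 may reduce the number of usable controls, and the conclusion may be more cautious. Dating the ward protocols is the most valuable step, because the trend model is too imprecise to settle the question alone.
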